#### Nutritional status

Prior to the initial consultation by the dietitian, only the prehabilitation group will complete a 3-day dietary diary to estimate energy and protein intake.

To assess nutritional status, the following measurements will be performed at baseline and the week prior to surgery in both groups. Weight and height will be measured to calculate the body mass index (BMI). To screen for malnutrition, the Patient-Generated Subjective Global Assessment (PG-SGA) will be completed at baseline and the week prior to surgery (Ottery 1996; Sealy et al. 2018). To determine body composition, a standardised bioelectrical impedance analysis (BIA) with a single-frequency 50-kHz impedance metre (Bodystat 500, Bodystat, Isle of Man, UK) will be performed. Different equations will be used to calculate fat-free mass (FFM): Kyle when BMI < 30 (Kyle et al. 2003), Horie with a BMI ≥ 30 (Horie et al. 2011) and Rutten in case of chronic obstructive pulmonary disease (Rutten et al. 2010). Finally, the hand grip strength will be determined by the dietitian with a hand-held hydraulic dynamometer (Jamar, Patterson Medical, Warrenville, IL, USA). The measurement will be repeated three times, and the highest result of both hands will be recorded.

#### Mental health status

The psychological assessment be determined using the Hospital Anxiety and Depression Scale (HADS) (Zigmond and Snaith 1983), consisting of a 7-item subscale to assess complaints of anxiety and depression, and the Insomnia Severity Index (ISI) (Bastien et al. 2001), assessing sleeping disturbances. In the prehabilitation group only, during a consultation with a clinical psychologist, the results of these questionnaires will be discussed. Since the score of the HADS is not expected to change in a limited period of 2 to 3 weeks, it will only be completed at baseline. The ISI will be completed at baseline, the week prior to surgery and 3 months after surgery.

#### Quality of life: assessing patient empowerment

Quality of life will be assessed at baseline, 6 weeks and 3 months after surgery, using the following questionnaires sent by email:EQ-5D-5L (EuroQol group, 5-level general health-related quality-of-life questionnaire (Herdman et al. 2011; Euroqol Group n.d.)EORTC QLQ-C30 (European Organisation for Research and Treatment of Cancer; quality of life of cancer patients (Aaronson et al. 1993; European Organisation for Research and Treatment of Cancer n.d.)EORTC QLQ-LC13 (European Organisation for Research and Treatment of Cancer; quality of life of cancer patients — lung cancer specific (European Organisation for Research and Treatment of Cancer n.d.; Bergman et al. 1994)

Additionally, a patient satisfaction questionnaire assessing all items of the programme is drafted by the research team and will be sent by email to both groups the week prior to surgery and 3 months postoperatively.

#### Respiratory status

Pulmonary functioning will be assessed according to standard of care. Additionally, the maximal inspiratory pressure (MIP) will be measured with the MicroRPM (respiratory pressure meter, CareFusion, San Diego, CA, USA) in order to determine the intensity of the inspiratory muscle training, which will be elaborated further in the “interventions” section. The MIP will be measured three times, aiming for a difference less than 5%. The highest pressure will be recorded and used for the programme. The MIP will be determined at baseline, the week before surgery and 6 weeks postoperatively.

#### Cost-effectiveness

Finally, to estimate the cost-effectiveness of the multimodal prehabilitation programme, a shortened institute for Medical Technology Assessment (iMTA) questionnaire (Bousema et al. 2018) will be used, consisting of the iMTA Productivity Cost Questionnaire (iPCQ) and the iMTA Medical Consumption Questionnaire (iMCQ). Patients will be requested to fill out the iPCQ and iMCQ at baseline and 3 months after surgery.

### Interventions

The 3-week multimodal prehabilitation programme commences after the baseline assessment and finishes 3–4 days before surgery. The programme contains six pillars: exercise programme, nutritional support, psychological support, smoking cessation, patient empowerment and respiratory optimisation (disease specific optimisation).

#### Exercise programme

The exercise programme consists of in-hospital, supervised training on three nonconsecutive days per week, for about 60 min, consisting of high-intensity interval training (HIIT) endurance training and strength exercises. Patients will be supervised by a physiotherapist, specialised in oncology and preferably train in peer groups if permitted by the periodicity of inclusion of subjects and existing COVID-19 measures. The intensity of the exercise programme will be individualised based on the baseline assessment and will be continuously evaluated by the physiotherapist during the programme.

The HIIT will be performed on a bicycle ergometer and consists of two series of eight repetitions of uninterrupted cycling. One repetition consists of 30 s of strain, set on 65% of the MSEC measured with the SRT, followed by 30 s of rest being 30% of the MSEC. Intensity of the HIIT will be monitored and adjusted, if necessary: if a patient scores ≤ 11 on the Borg scale (Achttien et al. 2011), the intensity will be increased by 5%; intensity will be decreased by 5% when the Borg score is ≥ 15 or when a patient will not be able to complete the eight repetitions.

The supervised strength exercises will be performed on fitness devices, and the intensity will be based on the 1-RM strength test calculation at baseline. The intensity will start with 65% of 1-RM in week 1, will increase to 70% in week 2 and if time allows 75% in week 3. Strength training will consist of two series of ten repetitions of the following exercises, targeting major muscle groups: lateral pull down, leg press, chest press and low row.

Finally, patients will be instructed by the physiotherapist to perform out-of-hospital exercises — like walking or cycling, according to patient preference — with low to moderate intensity, on the remaining 4 days of the week for at least 60 min per day.

#### Nutritional support

Nutritional status will be optimised through nutritional counselling by a registered dietitian. Based on the baseline assessment, the dietitian will provide a tailored dietary advice, including energy and protein requirements. Energy intake will be based on the calculated energy expenditure. The recommended daily protein intake is 1.9–2.2 g of protein/kilogram FFM (as determined with BIA). When FFM cannot be calculated, actual body weight will be used with a daily protein recommendation of 1.5–1.8/kg.

All patients in the prehabilitation group will receive a high-quality protein powder supplement containing whey and casein proteins, providing 10 g of essential amino acids — of which 2 to 3 g of leucine — per portion of 30 g (Refit®-TMP-90-Shake, Friesland Campina Domo, Amersfoort, the Netherlands). Patients will be instructed to ingest 30 g of supplement within 1 h after the in-hospital supervised training and daily 1 h before going to sleep.

Additionally, vitamin D and multivitamin supplements will be provided for daily use. Vitamin D dosage depends on age, gender, skin type and sun exposure and is based on the guideline of the Health Council of the Netherlands (Vitamin D guideline, Health Council of the Netherlands n.d.).

#### Psychological support

Psychological support will consist of a 45-min explorative consultation by a clinical psychologist. During this consult, burden of the disease and accompanied treatment as well as the patient’s coping strategies will be assessed, and when indicated, empowerment or psychoeducation will be provided. The clinical psychologist will determine whether follow-up sessions are needed during the perioperative phase and/or referral to a psychiatrist is indicated and will act accordingly. Furthermore, breathing and relaxation techniques, assisted with audio, will be provided to the patients.

#### Smoking status

If applicable, patients will be offered to follow a smoking cessation programme. This consists of counselling and nicotine replacement therapy and is outsourced to a specialised institute in the Netherlands (SineFuma Private Company, Breda, the Netherlands) (SineFuma n.d.).

#### Patient empowerment

To maximise patient empowerment, participants will be optimally informed and educated about the prehabilitation programme, the surgical care pathway and their own contribution. An information booklet containing information on all interventions of the programme will be handed out; a logbook will be provided to register all study-related activities.

#### Respiratory optimisation (disease-specific optimisation)

Disease-specific optimisation is directed at the affected organ system: the respiratory system in the case of NSCLC. During the in-hospital supervised sessions, patients will perform inspiratory muscle training (IMT). An IMT device (Philips-Respironics Threshold IMT, Philips, Eindhoven, the Netherlands) will be provided to the patient and intensity will be based on the MIP assessment at baseline. The training starts at 40% of the MIP and will increase to at least 50%. The patient will receive instructions from the physiotherapist how to perform the exercise at home. Training will be performed twice daily for 15 min. Additionally, breathing and sputum clearance techniques will be taught by the physiotherapist prior to surgery.

### Outcome measures

#### Primary outcomes

The main primary outcome of this study is feasibility of the prehabilitation programme. Feasibility is defined as ≥ 80% protocol adherence (per intervention) of at least 80% of the participants in the prehabilitation group. To determine feasibility, we will collect the following data: number of eligible patients, number of patients enrolled, number of drop outs, number of attended supervised training sessions (per patient), patient’s logging booklet (number of out-of-hospital low to moderate training, recorded intake of nutritional supplements) and activity monitor data. The second primary outcome is functional capacity. Functional capacity will be determined at baseline, the week prior to surgery and 6 weeks postoperatively. Change over time compared to baseline within and between groups will be determined.

#### Secondary outcomes

The following secondary outcomes will be studied:Programme evaluation as a whole and per intervention (based on compliance, patient satisfaction and experience of the research team)Effect on clinical outcome: 30-day mortality, length of hospital stay, 30-day complication rate expressed as the comprehensive complication index (Slankamenac et al. 2013) and readmission rate. This will be compared to the control group and a historical Dutch cohort as recorded in the DLCAs (Dutch Institute and for Clinical Auditing n.d.).Cost-effectiveness of the prehabilitation programmeEfficacy of the programme on nutritional and mental health status, smoking cessation and quality of life compared to baseline and control groupCorrelation between VO2max estimated with the physical condition questionnaire (FitMax^©^) and as determined with the SRT and, if applicable, CPET

### Data handling

With the use of an electronic case report form (eCRF), a database was built in castor electronic data capture (EDC) (Castor EDC n.d.). Castor EDC complies with Title 21 of the Code of Federal Regulations Part 11, General Data Protection Regulation (GDPR) and is fully ISO (International Organization for Standardization) 27001, 27002 and 9001 certified. When a new patient will be registered in castor EDC, patient codes are automatically generated, complying with the GDPR. Most of the data from the assessments will be entered directly into the eCRF. The remaining data will be entered by members of the research team in both centres. To guarantee the quality of this study, monitoring will be executed by an independent party appointed by the sponsor. All data saved in Castor EDC and source files will be stored for a period of 15 years.

### Statistical analysis

Because of the sample size of the group, descriptive data will be presented as median (interquartile range and/or range). Categorical data will be presented as numbers and percentages. Results of validated questionnaires will be calculated, and missing data will be handled using the instructions from the original authors. Missing data which will be used in the definition of feasibility will be considered as “not performed”.

Feasibility will be descriptively evaluated (group level and patient level), both dichotomously (yes/no) and as percentage of the total number of offered interventions.

Comparative outcomes, such as functional capacity, between the different test moments will be compared within the group participating in the multimodal prehabilitation programme and within the control group with the Friedman test and between groups with the Mann–Whitney *U*-test. Nonparametric tests will be used because of the small sample size. Dichotomous data will be compared between groups with chi-square test. Mixed model analyses will be used to evaluate functional capacity over time.

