**Methods:**

The multimodal prehabilitation programme consists of an exercise programme, nutritional support, psychological support, smoking cessation, patient empowerment and respiratory optimisation. In two Dutch teaching hospitals, 40 adult patients with proven or suspected NSCLC will be included. In a non-randomised fashion, 20 patients follow the multimodal prehabilitation programme, and 20 will be assessed in the control group, according to patient preference. Assessments will take place at four time points: baseline, the week before surgery, 6 weeks postoperatively and 3 months postoperatively. Feasibility and indicative evidence of efficacy of the prehabilitation programme will be assessed as primary outcomes.

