### Participants

All consecutive patients meeting the inclusion criteria will be asked to participate in the multimodal prehabilitation programme. Patients are deemed eligible when ≥ 18 years of age, with pathologically confirmed or suspected NSCLC and an indication for anatomical lung resection. Furthermore, a straightforward preoperative work-up is needed to ensure patients can enter the programme directly after diagnosis in order to use the window of opportunity between diagnosis and surgery as efficient as possible. Also, the ability to provide written informed consent is needed for inclusion. Eligible patients not willing to participate in the multimodal prehabilitation programme will be asked to participate in the control group. The control group may provide insight in the course of functional capacity perioperatively and will enable comparison with the prehabilitation group.

Exclusion criteria comprise a contra-indication for training, renal insufficiency (defined as estimated glomerular filtration rate (eGFR) < 60 ml/min/1.73 m^2^) or participation in other trials that may interfere. Referred patients from another hospital with the diagnostic phase already completed will be excluded, for logistical reasons, travel distance and the probability that these factors may affect feasibility of the programme. If a contra-indication for training will become apparent after signing informed consent and following baseline assessment, we intend to exclude the subject from participation for safety reasons. Furthermore, if the postoperative pathology results will not confirm the diagnosis NSCLC, the data of this patient will be included in the analysis; however, we intend to recruit an extra patient to finally include a total of 40 patients with confirmed NSCLC, per centre ten patients in the prehabilitation group and ten in the control group. All assessed patients will be logged.

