## Discussion

Since many disciplines are involved and time is limited, multimodal prehabilitation is a logistic challenge. It is widely studied in patients with colorectal cancer and deemed feasible and effective (Rooijen et al. 2019; Trepanier et al. 2019; Scheede-Bergdahl et al. 2019). However, in the Netherlands, the recommended treatment interval for NSCLC is shorter compared to colorectal cancer due to tumour biology and mutual agreements amongst scientific societies and the DICA.

However, especially, the NSCLC population may particularly benefit from prehabilitation. The pulmonary system is one of the determinants of cardiorespiratory fitness, a measure interpreted as the reflection of total body health (Ross et al. 2016), as well as the organ system affected by NSCLC. Furthermore, the lung is the organ that is resected during surgery, thereby further compromising cardiorespiratory fitness in itself. Although improving cardiorespiratory fitness preoperatively will not prevent a decrease of functional capacity postoperatively, prehabilitation may limit the extent.

This protocol is a result of an extensive multidisciplinary project. Two clinical groups with expertise in perioperative recovery optimisation developed a protocol based on experience and available evidence, combining various interventions within a short timeframe. In order to make a patient-friendly programme, all disciplines need to optimise and harmonise planning.

To our knowledge, only one randomised controlled trial with a multimodal prehabilitation programme in a NSCLC population has been published; however, this concerned a non-supervised home-based programme with less interventions compared to our study (Liu et al. 2020). In the Netherlands, we experience a growing interest in prehabilitation prior to surgery, yet to date, there are no formal public prehabilitation programmes available for NSCLC surgery patients.

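### Recruitment is fixed at ten per group in each hospital, but the feasibility reporting and the named rank and chi-square tests make no use of centre

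*Protocol article*

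**What the plan says.** The Abstract gives the size and the allocation: "In two Dutch teaching hospitals, 40 adult patients with proven or suspected NSCLC will be included", and "In a non-randomised fashion, 20 patients follow the multimodal prehabilitation programme, and 20 will be assessed in the control group, according to patient preference". The Participants section adds the split by hospital: "per centre ten patients in the prehabilitation group and ten in the control group". These are recruitment targets counted in patients with confirmed NSCLC.

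The main primary outcome is set on the whole intervention arm: "Feasibility is defined as ≥ 80% protocol adherence (per intervention) of at least 80% of the participants in the prehabilitation group". The Statistical analysis section names the levels at which it will be looked at: "Feasibility will be descriptively evaluated (group level and patient level), both dichotomously (yes/no) and as percentage of the total number of offered interventions". Hospital is not one of them.

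For functional capacity, the second primary outcome, the comparison is "within the control group with the Friedman test and between groups with the Mann–Whitney" U-test. For binary outcomes, "Dichotomous data will be compared between groups with chi-square test". Neither mentions centre. The same section also plans mixed models for functional capacity over time, without listing their terms.

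The Discussion describes what could make the programme infeasible: "Since many disciplines are involved and time is limited, multimodal prehabilitation is a logistic challenge". The Background and the Discussion both say that the article should help other hospitals set up a similar programme.

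**The concern.** Allocation follows patient preference, so hospital is the only factor on which the two groups are meant to be balanced by design. The stated analysis does not use it, and this matters in two ways.

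**Feasibility.** If the obstacle is organising many disciplines in a short time, adherence depends partly on the hospital. A reader elsewhere wants to know whether the programme ran in both hospitals or mainly in one. The pooled count cannot say.

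**Functional capacity.** If the analysed variable differs between hospitals, an unstratified rank test leaves that difference in the noise although the groups are balanced on it. The test then falls below its nominal level and loses power, which a study of 40 can ill afford.

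**Working it through.** **Inputs from the article:** two hospitals; 10 prehabilitation and 10 control patients in each; the 80%/80% rule; Mann–Whitney test between groups.

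**Assumed, because the article gives no value:** true patient-level adherence in each hospital; a 0.8 SD group effect; the size of the centre difference; a two-sided 5% level; normally distributed data.

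**The article's own figure.** 2 × (10 + 10) = 40, as stated.

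**Feasibility count.** 80% of 20 = 16 adherent patients, applied to each intervention separately. The ways to reach exactly 16 with ten patients per hospital are 8 + 8, 9 + 7 and 10 + 6. If one hospital has 5, the other would need 11, which is impossible. So 6 of 10 is the lowest count that the pooled rule can pass.

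**How often this could happen.** Let X and Y be independent Binomial(10, p) counts for the two hospitals. The pooled rule passes when X + Y ≥ 16.

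| True adherence, hospital A / B | P(pooled pass) | P(B reaches 8 of 10) | P(pooled pass and one hospital below 8) |
|---|---|---|---|
| 95% / 65% | 0.63 | 0.26 | 0.37 |
| 100% / 60% | 0.63 | 0.17 | 0.47 |
| 80% / 80% | 0.63 | 0.68 | 0.17 |

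The pooled pass probability is 0.63 in all three rows, so the pooled verdict does not tell them apart. The last row also shows the limit of ten patients: a hospital truly at 80% misses 8 of 10 with probability 1 − 0.68 = 0.32.

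**Rank test.** With two equal centres that differ by c within-group SDs, centre explains a share f = (c²/4) / (1 + c²/4) of the variance, so c = 2√(f/(1 − f)). For f = 10%, 20% and 30%, c = 0.67, 1.0 and 1.31. Simulated trials with 10 v 10 in each centre give:

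| Centre difference (SD) | Mann–Whitney level | Power, Mann–Whitney | Power, van Elteren | Loss (points) |
|---|---|---|---|---|
| 0 | about 5% | 67% | 66% | −1 |
| 0.67 | 3.8% | 62% | 66% | 4 |
| 1.0 | 2.8% | 57% | 66% | 9 |
| 1.31 | 1.9% | 50% | 66% | 16 |

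The power columns assume the 0.8 SD effect. At a centre difference of 0.5 SD and an assumed effect of 0.9 SD, the Mann–Whitney level is 4.4% and power is 75% against 76% for the stratified test. The stratified test holds its level at about 5% throughout.

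**The case against.** Five objections deserve weight.

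- **Level shifts cancel.** The Primary outcomes section defines the second primary outcome as change from baseline. A constant difference between hospitals in equipment or staff drops out of a change score. The power figures then apply only if the hospitals differ in mean change. The Physical status section also describes a standardised walk test and a calibrated ergometer, which makes large shifts less likely. This stands, and it makes the rank-test part conditional.
- **Silence is not exclusion.** A reader might infer that every between-group comparison pools the hospitals. The article does not say so. The mixed model's terms are not given, so centre may be among them, and a full protocol or SAP that is not shown could add it. What remains is narrower: the feasibility criterion, its reporting levels and two named tests are written down, and none of them uses centre.
- **A quota is not a randomisation stratum.** No analyse-as-randomised argument applies. The balance may not be exact either, because patients without confirmed NSCLC stay in the analysis and are replaced. The larger threat is preference-based allocation, which the authors acknowledge and which stratifying by centre does not cure. This stands, but it does not remove the gain from using a nearly balanced factor.
- **Masking is limited.** A hospital at 5 of 10 or fewer cannot pass unnoticed, and patient-level reporting does not rule out a display by hospital. This stands; the exposed range is 6 or 7 of 10.
- **Ten patients cannot carry a verdict.** It is tempting to demand 8 of 10 in both hospitals. With no centre difference at all, that would cut the chance of a pass from 0.63 to 0.68² = 0.46 at true 80%, and from 0.83 to 0.67 at true 85%. Nor would an observed 6 of 10 show that the programme failed there. The per-centre figures should therefore be descriptive.

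**Conclusion.** The point holds as a modest improvement to methods the article states; it does not show an error. The feasibility part is plain arithmetic: a pooled 16 of 20 may be 8 + 8, 9 + 7 or 10 + 6, and the planned reporting levels do not separate them. How likely a masked imbalance is depends on assumed adherence rates.

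The rank-test part rests on an assumed centre difference. From about 0.7 SD in the analysed variable, the unstratified test is conservative (level about 2–4%) and loses roughly 4–16 points of power at a 0.8 SD effect. Below about 0.5 SD the loss is negligible. A reader might conclude that the planned test is conservative as a matter of fact. The article gives no centre difference, so it does not support that.

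**What to change.** 1. Keep the pooled 80%/80% rule as the feasibility verdict. Beside it, report for each hospital the adherence percentages and the number of adherent patients per intervention, as description only and with no pass mark per hospital.
2. Replace the unstratified Mann–Whitney test between groups by the van Elteren test stratified by centre.
3. State that the mixed model for functional capacity includes centre as a fixed effect.

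No new data are needed. The cost is one extra table column and about 1 point of power for the rank test if the hospitals do not differ. The feasibility verdict itself is unchanged.

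### The within-group Friedman test over three visits can turn significant through the expected postoperative decline alone and does not estimate the promised change from baseline; two named paired contrasts should replace it

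*Protocol article*

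**What the plan says.** The Statistical analysis section opens its comparative part with "Comparative outcomes, such as functional capacity, between the different test moments will be compared" and then names the within-group method: "within the group participating in the multimodal prehabilitation programme and within the control group with the Friedman test". Between groups it names the Mann–Whitney test, and it adds mixed models for functional capacity over time. No pairwise contrast is attached to the Friedman test.

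Under Primary outcomes, the visits are fixed: "Functional capacity will be determined at baseline, the week prior to surgery and 6 weeks postoperatively". The target quantity is fixed there too: "Change over time compared to baseline within and between groups will be determined".

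The Discussion states the expected course after resection: improving fitness beforehand "will not prevent a decrease of functional capacity postoperatively, prehabilitation may limit the extent".

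For the nutritional measures, the Nutritional status section says that "the following measurements will be performed at baseline and the week prior to surgery in both groups". These therefore have two visits, not three.

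Group size comes from the Abstract: "20 patients follow the multimodal prehabilitation programme, and 20 will be assessed in the control group".

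**The concern.** The stated target is change from baseline. The Friedman test ranks the visits within each patient and asks whether any visit tends to rank differently from the others. It returns one p-value, with no estimate, no direction and no indication of which visit is responsible. One of the three visits follows lung resection, and the authors themselves expect a decrease there. A significant result in the prehabilitation group is therefore compatible with a preoperative gain, a surgical loss, or both.

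The risk is in interpretation. A significant within-group result could be taken as indicative evidence that the programme improved capacity when it reflects the operation.

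Two further consequences follow from the choice of test. The standard Friedman test needs a complete set of visits, so a patient not tested at 6 weeks also drops out of this analysis with usable baseline and pre-surgery values. And where a measure has only two visits, the test loses efficiency against the usual paired alternative.

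**Working it through.** The article gives no alpha, effect size, SD or power for this comparison, so there is no figure of its own to reproduce. The check is a simulation.

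**Inputs from the protocol:** three visits (Primary outcomes) and 20 patients per group (Abstract).

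**Assumptions:** two-sided 5% level; normal data with equal SD at each visit; a common between-visit correlation ρ; a fall at 6 weeks expressed in SDs of the outcome.

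**Test statistic.** For n patients, k visits and rank sums R_j,

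Q = 12/(n·k·(k+1)) · ΣR_j² − 3n(k+1), referred to chi-square with k−1 degrees of freedom.

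**Step 1: no preoperative change, only a 6-week fall (n = 20; 20,000 samples for Friedman, 4,000 for Wilcoxon).** Entries for the fall columns are Friedman rejection rates.

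| ρ (assumed) | no fall | 0.1 SD | 0.3 SD | 0.5 SD | Wilcoxon, baseline vs pre-surgery |
|---|---|---|---|---|---|
| 0.6 | 5% | 7% | 24% | 57% | about 5% throughout |
| 0.8 | 5% | 9% | 43% | 86% | about 5% (4–5%) |
| 0.9 | 5% | 13% | 73% | 99% | about 5% (4–5%) |

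The Friedman test holds its 5% level when nothing changes at any visit. Its rejections in the other columns are correct for its own null hypothesis, but they say nothing about a preoperative gain.

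**Step 2: can the p-value tell gain from loss?** Here effects are in SDs of the within-patient change, which equals √(2(1−ρ)) outcome SDs. At ρ = 0.8 that is √0.4 = 0.63, so a 0.5 SD fall in the outcome is 0.5/0.63 = 0.79 change-SDs. With n = 20:

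- gain of 0.75 before surgery and no loss at 6 weeks: Friedman rejects in 82%;
- no gain and a loss of 0.75 at 6 weeks: Friedman rejects in 83%.

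The two cases cannot be told apart from the test result.

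**Step 3: incomplete visits.** Assume ρ = 0.8, a true gain of 0.4 SD and a return to baseline at 6 weeks. With 20 complete patients, Friedman has about 68% power and Wilcoxon on baseline to pre-surgery about 74%. If 3 of 20 (assumed) miss only the 6-week test, Friedman runs on 17 patients and falls to about 57%. The Wilcoxon test still uses all 20.

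**Step 4: two visits.** Put k = 2 and let S be the number of patients whose first visit ranks higher. Then R_1 = n + S and R_2 = 2n − S, and

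Q = (2/n)(5n² − 2nS + 2S²) − 9n = (n − 2S)²/n,

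which is the sign-test statistic. For normal data the asymptotic efficiency relative to a paired t-test is 2/π for the sign test and 3/π for the signed-rank test. The ratio is 2/3, so the sign test has about two-thirds of Wilcoxon's efficiency.

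**Step 5: the between-group alternative.** With 20 against 20, no gain and a common loss of 1 change-SD, a comparison of baseline to pre-surgery change rejects in about 5%. For a gain of 1 change-SD its power is about 84% (Mann–Whitney) or 87% (group-by-time contrast). For 0.75 it is about 61% or 64%.

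**The case against.** The strongest reply is that Friedman does not stand alone. The same paragraph plans Mann–Whitney tests and mixed models, and Primary outcomes promises change from baseline between groups. These can isolate the preoperative change in functional capacity and keep patients who miss the 6-week visit. The control group is there to show the usual perioperative course. This stands, and it rules out the reading that the plan cannot show a prehabilitation gain. That is true only of the Friedman p-value. Running Friedman in the controls as well does not rescue it, because setting two within-group p-values side by side does not test a difference.

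A second reply is that pairwise follow-up tests are detail for an analysis plan that is not shown. That is fair for follow-up tests, but the omnibus test is what the article names, and it does not match the article's own target of change from baseline.

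Third, some stronger claims a reader might infer are not supported:

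- **That the test will be significant because of surgery.** This depends on a fall and a correlation the article does not give. At 0.1 SD and ρ = 0.8, rejection is only 9%.
- **That every patient is expected to decline.** The Discussion makes a general statement, not one about each patient.
- **That only the preoperative interval matters.** The Discussion also hopes to limit the postoperative decrease, so the 6-week change is of interest in its own right.
- **That Friedman is generally underpowered.** With complete data the loss in Step 3 is modest and belongs to one trajectory. If capacity ends 0.3 SD below baseline after a 0.4 SD gain, Friedman rejects more often than Wilcoxon (96% against 74%), partly because of the surgical loss.

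Finally, this is a feasibility study whose main primary outcome is descriptive, and it seeks only indicative evidence of efficacy. That limits the consequence but does not make the named test suitable.

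**Conclusion.** The point holds for the within-group Friedman test and not for the analysis plan as a whole. A significant result cannot be read as a preoperative gain. With 20 patients and no such gain, it arises in about 57% to 86% of studies for a 0.5 SD postoperative fall at correlations of 0.6 to 0.8, and in about 24% to 43% for a 0.3 SD fall, against about 5% for a direct baseline to pre-surgery test. These rates rest on assumed falls, assumed correlations and normal data. The qualitative conclusion, that the test gives neither visit nor direction, needs none of these assumptions. The complete-visit requirement and the reduction to a sign test for two-visit measures are lesser, additional reasons to change the method. The main feasibility outcome is unaffected.

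**What to change.** In the Statistical analysis section, replace Friedman as the within-group method with two prespecified contrasts per group: baseline to pre-surgery, and baseline to 6 weeks. For functional capacity, estimate them with 95% CIs from the mixed model already planned, or use the Wilcoxon signed-rank test with a Hodges–Lehmann estimate and 95% CI on all patients who have the two visits concerned. For measures taken at two visits only, name the Wilcoxon signed-rank test. State that conclusions about efficacy rest on the between-group difference in change and not on a comparison of within-group p-values. That difference remains open to the selection and confounding that the Discussion acknowledges for the non-randomised design.

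The cost is analysis wording only, with no new data or visits. The one trade-off is two tests per group in place of one omnibus test, so the contrasts should be named in advance and reported mainly as estimates with intervals.
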